# Comparison of intradialytic neuromuscular electrical stimulation and oral nutritional supplements in hemodialysis patients: study protocol for a multicenter, parallel-group, randomized controlled trial in Korea

**DOI:** 10.1186/s13063-021-05918-x

**Published:** 2021-12-20

**Keywords:** Hemodialysis, Neuromuscular electrical stimulation, Muscle strength, Physical function, Protein supplementation, Quality of life

## Abstract

**Background:**

The prevalence of sarcopenia increases as renal function decreases, and a considerable number of hemodialysis (HD) patients have sarcopenia. Exercise and nutritional support are established interventions to prevent and treat sarcopenia. Recently, many studies evaluating intradialytic neuromuscular electrical stimulation (NMES) showed improvement of muscular strength and mass, functional capacity, and quality of life (QOL). However, there has been no research about the effect of simultaneous nutritional support and NMES in HD patients.

**Methods:**

This is a 12-week, randomized controlled, parallel-group, multicenter trial of intradialytic NMES and protein supplementation for HD patients. Seventy-two patients receiving HD will be randomly assigned in a 1:1:1:1 ratio to control, intradialytic NMES only, protein supplementation only, and intradialytic NMES combined with protein supplementation groups. NMES will be delivered to a total of four areas of the bilateral vastus medialis and vastus lateralis using a 4-channel NMES instrument. A total of 25 g of protein supplements will be provided at the beginning of every dialysis session or after the NMES. The primary endpoint is the difference of hand grip and leg muscle strength at 12 weeks among 4 treatment groups. Secondary endpoints include muscle mass, physical performances, and questionnaires about QOL and physical activity.

**Discussion:**

In this study, we will evaluate the differential effectiveness of nutritional support and NMES during HD on muscle strength, muscle mass, physical function, and QOL. We expect that this study can provide guidelines for a new therapeutic option for HD patients who are unable or hesitant to exercise. Furthermore, this option can offer an opportunity to improve the physical function, QOL, and prognosis of HD patients.

**Trial registration:**

Clinical Research Information Service (CRIS), Korea, KCT0005573. Retrospectively registered on 03 November 2020

## Introduction

Hemodialysis (HD) is a type of renal replacement therapy that removes fluid, electrolytes, and uremic toxins that have accumulated in the body due to reduced kidney function. There are approximately 80 thousand (1497.6 patients/million population) end-stage renal disease (ESRD) patients receiving HD in Korea, and the number of patients has been increasing by 5–8% annually.

Sarcopenia is characterized by loss of muscle mass and strength, and decreased quality of life (QOL) with age, morbidities, and immobility and is associated with protein-energy wasting (PEW) in chronic kidney disease (CKD) and ESRD patients [1]. Sarcopenia is also associated with functional decline, increased risk of falling, and increased mortality in CKD and ESRD patients [2, 3]. In addition, sarcopenia in dialysis patients is associated with depression leading to decreased survival [4].

The prevalence of sarcopenia in HD patients varies from 21 to 68% depending on the methodology and demographics [5]. CKD-associated catabolic alterations can explain the profound features of sarcopenia in CKD patients [6]. CKD is associated with chronic low-grade inflammation leading to progressive weight loss, muscle weakness, and loss of the ability to exercise. Inflammatory cytokines and inactivity-mediated destruction of protein homeostasis result in the catabolic destruction of structural and functional proteins, resulting in skeletal muscle wasting [7]. These changes are highly pronounced in dialysis patients due to fatigue, inactivity, and the catabolic effect of the HD procedure itself [8–13].

There have been many approaches to treat sarcopenia, and exercise and nutritional support were effective as prevention and treatment strategies for sarcopenia [14], although study outcomes were inconsistent due to the differences in exercise dose, use of nutritional supplementation, and baseline nutritional status [15–17]. A review pointed that nutritional supplementation and exercise should be prescribed at the right patient (a patient who is at risk or with PEW and can tolerate and benefit from the exercise), right time (when the catabolism is at its peak or in between meals and when the patient’s stamina is the highest), and right dose (nutritional supplementation with amount and mixture that allow most efficacy and beneficial exercise intensity but not ineffective or even harmful), and recommended both interventions as a part of healthy lifestyle modification [18].

Protein servings are often deficient in the Korean diet. The Korea National Health and Nutrition Examination Survey (KNHANES) 2012–2016 data showed 40.5% and 59.9% of males and females older than 75 years took protein less than the estimated average requirements. Many patients receiving dialysis maintain the protein-restricted diet due to the fear of hyperkalemia and hyperphosphatemia. And several studies reported that protein intake was less than 1.0 g/kg/day in about half of HD patients [19, 20]. The typical dietary protein intake recommendation for ESRD patients is 1.2 g/kg/day [21]. However, some experts recommended a dietary protein intake of more than 1.8 g/kg/day in dialysis patients because they do not have to prevent CKD progression and are in a hypercatabolic state due to dialysis itself [22]. Protein supplementation during dialysis improved body composition and physical function and reduced inflammatory markers [23, 24]. Short-term oral energy or protein/amino acid supplementation improved nutritional status by increasing serum albumin levels and BMI without influencing serum potassium levels in dialysis patients in a meta-analysis [25]. In addition, renal-specific oral nutritional supplementation with a low-protein intake prevented a decline in nutritional status and quality of life without increasing the need for phosphorus binders [26].

Exercise is an anabolic-based strategy along with nutritional support, anabolic steroids, and growth hormones. Net protein catabolism occurs when protein and energy intake are inadequately low. However, resistance training during protein restriction counteracts impaired muscle cell metabolism [27]. Exercise improves muscle size, protein synthesis rate, neuromuscular function, insulin sensitivity, and inflammation associated with increased insulin-stimulated glucose and amino acid transport [3, 28].

However, physical inactivity is an important clinical problem among dialysis patients [27]. The Kidney Disease Outcome Quality Initiative (K/DOQI) and European guidelines recommend that nephrologists counsel and encourage dialysis patients to increase physical activity [29, 30]. Providing exercise therapy to patients who are unable to perform conventional dynamic training due to position limitations, hemodynamic instability during dialysis, low motivation, or fatigue is a major challenge [31]. HD patients, especially elderly patients, reported low levels of physical activity, which is associated with poor physical function and frailty [32].

Intradialytic exercise (IDE) can enhance or replace physical exercise in frail and exercise-hesitant HD patients. Neuromuscular electrical stimulation (NMES) induces muscle contraction by stimulating muscles or peripheral nerves, which prevents muscle atrophy due to central or peripheral muscle paralysis. NMES has the strength of application to exercise-hesitant patients. Recently, many studies have evaluated the feasibility and efficacy of intradialytic NMES. Intradialytic NMES of the quadriceps or gluteal muscles improved muscular strength, muscle cross-sectional area, functional capacity, and quality of life [33, 34]. Intradialytic NMES improved cardiorespiratory reserves (VO_2_ peak, VO_2_ anaerobic threshold) and muscle strength [31]. It also improved physical functioning and health-related QOL [35]. In addition, intradialytic NMES altered inflammatory markers, as it increased the levels of IGF-1, reduced the levels of IL-10, and reduced DNA damage in blood [36, 37]. Therefore, intradialytic NMES can also be a good option to enhance muscle strength and physical functioning as well as exercise compliance in HD patients, especially exercise-hesitant patients.

However, there has been no research about the effect of simultaneous nutritional support and NMES in dialysis patients. Therefore, we designed a 12-week trial comparing control, protein supplementation only, intradialytic NMES only, and intradialytic NMES combined with protein supplementation. In this study, we will evaluate the differential effectiveness of nutritional support and NMES during HD on muscle power, muscle mass, physical function, and QOL.

## Methods/design

### Study design

The study protocol was designed in accordance with the SPIRIT guidelines [38]. This is a 12-week, randomized controlled, parallel-group, multicenter trial of intradialytic NMES and protein supplementation for HD-dependent ESRD patients. Seventy-two patients receiving HD will be randomly assigned in a 1:1:1:1 ratio to the control, intradialytic NMES only, protein supplementation only, and intradialytic NMES combined with protein supplementation groups. Measurements will be scheduled for all patients at baseline and at follow-up every 4 weeks for 12 weeks; the measurements will include vital signs; blood and urine laboratory exams including total protein, albumin, total cholesterol, calcium, phosphorus, blood urea nitrogen (BUN), serum creatinine (SCr), total CO_2_, intact parathyroid hormone (PTH), highly sensitive C-reactive protein (hs-CRP), urine urea nitrogen/normalized protein catabolic rate (nPCR), and Kt/V; and body composition including bioelectric impedance study, physical performances, and questionnaires. Figure 1 presents a flowchart of the trial procedures.

**Fig. 1 Fig1:**
[figure not shown]
Clinical trial design

The primary endpoint was the difference in hand grip and leg muscle strength at 12 weeks among the 4 treatment groups. Secondary endpoints included the following: muscle mass; physical performance, including the 10-m walking test and timed-up-and-go test; and questionnaires about QOL, physical activity, depression, and falls.

### Recruitment and population

A total of 72 patients with ESRD receiving HD will be recruited in four tertiary hospitals in Korea.

Subjects will be eligible for inclusion in this study only if all of the following criteria apply: (1) stable ESRD patients who have been receiving HD for 3 months or more, (2) patients with serum albumin less than 4.0 g/dl and are suspicious of having PEW, and (3) patients who can thoroughly understand the protocol.

Subjects will be excluded for any of the following reasons: (1) acute kidney injury; (2) uncontrolled hypertension, diabetes, or heart failure; (3) aspartate aminotransferase (AST) or alanine aminotransferase (ALT) level 3 times or higher than the upper normal limit of the participating hospital; (4) hematologic or solid organ malignancies under treatment; (5) active infection; (6) positive for HIV/AIDS; (7) history of ischemic heart disease, stroke, or deep vein thrombosis within 3 months before participation; (8) planning to receive kidney transplantation within 3 months after participation; (9) contraindication to electronic stimulation including implantable defibrillator; (10) skin lesions around the electrical stimulation spots; (11) allergy to protein supplements; (12) history of participation in another clinical study within 2 months prior to study enrollment and plans to participate in another clinical study; and (13) researcher’s decision regarding inappropriateness of enrollment in the study.

All patients who are eligible for this study will be asked by study investigators. They will receive oral and written information from the investigator. The investigator will obtain written informed consent and the patient will be randomized.

As the participation in the study is voluntary, all participants are free to withdraw their consent to participate in the study at any time and for any reason without any further treatment or any consequences. Moreover, participation of any participants could be terminated by an investigator at any time, if an investigator believes it is in the best interest of the participant. We shall document the reasons and circumstances of the study discontinuation in the clinical record form.

### Randomization and concealment

The experiment will be conducted by block randomization (block size of 4; stratified block randomization schedule for 4 institutions; each institution has a separate randomization schedule); the blind code will be computer-generated by a statistician of an external organization (Seoul National University Hospital Medical Research Collaborating Center) using SAS®, who had no contact with participants. Only an independent physician assistant at the central coordinating institution will have the pregenerated codes, and all other research members will be blinded. Researchers call a central coordinating office for each patient assignment. Participants will be randomly assigned to the control (random code A), intradialytic NMES (random code B), protein supplementation (random code C), or intradialytic NMES combined with protein supplementation (random code D) for 12 weeks according to their assigned code, after they agree to enroll in the study and sign the informed consent form.

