### Quality control, data management, and monitoring

This study is organized by a team comprised of a principal investigator and co-investigators who take part in the design and implementation of the study. For quality control purposes, all the researchers will be trained to be well-acquainted with the study protocol and to perform tests in one unified way before the recruitment of participants. The interventions will be performed by one expert at each hospital. All data will be put onto a computer with password protection by a staff blinded to the group allocation. The original forms of data will be archived securely at the central coordinating institution. All the investigators will be responsible for data monitoring, which is performed after each subject’s participation is completed. Monitoring includes assessment of the progress of the study and verification of accuracy as well as the completeness of recorded data. After completion of the study, we will submit the original data and results to IRBs of participating institutions, and after the publication of results, we will disclose original data and results to the public. Audits will be held annually by the IRBs of participating institutions.

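### A fixed block size of 4 for four openly different arms, scheduled site by site, lets informed site staff deduce every fourth allocation

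*Protocol article*

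**What the plan says.** The randomisation scheme is in the protocol article, under Randomization and concealment: "The experiment will be conducted by block randomization (block size of 4; stratified block randomization schedule for 4 institutions", with its own schedule at each hospital. Under Study design, the allocation is equal across four arms: "Seventy-two patients receiving HD will be randomly assigned in a 1:1:1:1 ratio to the control, intradialytic NMES only, protein supplementation only", plus the combination arm. Under Recruitment and population: "A total of 72 patients with ESRD receiving HD will be recruited in four tertiary hospitals in Korea"; the split between hospitals is not given.

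On concealment, the article says: "Only an independent physician assistant at the central coordinating institution will have the pregenerated codes, and all other research members will be blinded". Researchers telephone a central office for each assignment once consent is signed, and the article prints which code letter stands for which arm.

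On visibility, NMES uses electrodes on both thighs during dialysis, three times a week, and the supplement is drunk at the dialysis session. Neither a sham nor a placebo is described. Under Quality control, data management, and monitoring: "The interventions will be performed by one expert at each hospital". The same section says that data entry is done by staff blinded to group.

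On discretion at entry, the last exclusion criterion is the "researcher’s decision regarding inappropriateness of enrollment in the study".

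**The concern.** When the number of arms equals the block size, each block is a single ordering of the four arms. If past assignments can be seen, the end of each block gives itself away. Here they can be seen: the interventions look different, one person per hospital delivers them, and the researchers who phone receive the assignments. Stratifying by site makes tracking easier, because staff need to follow only their own patients.

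What is at stake is selection at entry. Someone who expects a particular arm next can bring a patient forward, hold one back, or use the open-ended exclusion, all before the call is made. The planned size is 18 per arm, so a few selectively entered patients could move a group mean.

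A second, smaller matter is the statement that "all other research members will be blinded". Read literally, it cannot hold for those who deliver the interventions or receive the assignments.

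**Working it through.** **The plan's own figure.** The total of 72 sets the number of blocks, so it is reproduced first. Inputs from Sample size: difference 26.1 − (−8.3) = 34.4; SD 24.82; two-sided alpha 0.0083; power 80%; dropout 25%.

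n per group = 2 × (2.64 + 0.84)² × (24.82/34.4)² = 2 × 12.11 × 0.521 = 12.6, so 13. Then 13/0.75 = 17.3, so 18, and 4 × 18 = 72. The stated total is reproduced and is not in dispute.

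**Predictability within one block.** Take an observer who knows the block size and all earlier assignments at the site. The chance of naming the next arm correctly is:

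| Position in block | 1 | 2 | 3 | 4 |
|---|---|---|---|---|
| Chance | 1/4 | 1/3 | 1/2 | 1 |

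The mean over a complete block is (1/4 + 1/3 + 1/2 + 1)/4 = 2.083/4 = 52.1%. Without any information it is 25%.

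**Over the whole trial.** Each completed block at a site contains one fully determined allocation. The total is therefore (72 − R)/4, where R is the number of patients left in incomplete blocks, summed over the four sites.

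- Every site recruits a multiple of 4: R = 0, giving 18 (25%).
- Every site has three left over, the largest R possible: R = 12, giving 15 (21%).
- Assumed 18 per site: R = 8, giving 16 (22%). The third place in a block, a choice between two arms, also occurs 16 times.

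At 18 per site, the expected number of correct guesses per site is 4 × 2.083 + 1/4 + 1/3 = 8.92. That is 8.92/18 = 49.5%. The best-guess rate is therefore about 50–52%.

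**What varied block sizes would achieve.** This is a simulation of 1,500 sites of 18 patients. The observer guesses optimally, knows all earlier assignments and knows which sizes may occur, but not which one is in use.

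| Scheme | Known with certainty | Best-guess rate |
|---|---|---|
| Fixed 4 | 22% | 50% |
| 4 and 8, varied | about 6% | about 46% |
| 4, 8 and 12, varied | about 2% | about 44% |

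Staff who do not know the possible sizes would on average do no better than this observer.

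**How many patients remain.** Recruitment was planned from 26 October 2020 to the end of March 2022 (Trial status), which is 521 days. The article appeared on 20 December 2021, 101 days before the end. Assuming even accrual, 72 × 101/521 is about 14 patients, of whom 3 or 4 would be fully determined.

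**The case against.** The best defence is that the list is well protected. An outside statistician generates it, one independent person holds it, and each assignment is released by telephone after consent. That stands as far as the list goes. It does not prevent deduction from assignments already made and visible on the ward.

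Small blocks also protect balance when a site may have only about 18 patients, and that benefit is real. The plan's analysis of covariance and its mixed model adjusted for baseline imbalances would absorb some selection on measured baseline strength. They would not absorb selection on what is not measured, such as motivation or expected response.

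The timing argument stands in part. Publication came late in recruitment, so the printed block size itself exposes mainly the last patients. Whether site staff knew the size before then depends on the full protocol, which is not shown.

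A reader might infer more from the blinding sentence: that the article claims blinded participants or blinded strength testers, and so misleads about the primary outcome. The text does not support that. The sentence follows directly on who holds the codes, and can fairly be read as blinding to the list. It speaks of research members, not participants. No section says that the person giving NMES also measures strength, and none says that the statistician is blinded. Who measures strength is a detail that an article may leave to the full protocol.

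**Conclusion.** The point holds as a design weakness. Fixed blocks of 4 for four distinguishable arms, run per site, leave 15 to 18 of the 72 allocations (21–25%) open to certain deduction and give a best-guess rate of about 50–52%.

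This rests on two conditions: someone at the site knows the block size and the earlier assignments there, and the arms can be told apart as the article describes them. The second follows from the interventions as described. Knowledge of the block size is plausible but not documented before publication. The figure of 16 assumes 18 patients per site.

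Two stronger readings are not supported. One is that 18 determined allocations is the firm count; that requires every hospital to recruit a multiple of 4. The other is that selection bias has occurred; the documents show only that it could.

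The blinding sentence is wrong if taken literally for those who deliver the interventions or receive assignments, and loosely worded if it means the code list. Either way it needs correcting.

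**What to change.** 1. For patients not yet randomised, have the same external statistician issue new site schedules with block sizes varied at random in multiples of 4 (for example 4 and 8), and keep the sizes out of any document that site staff see. The main gain is in certain allocations; overall guessability falls only modestly, and some deduction remains possible. The simulated figures describe a full site of 18 and should not be applied to a short remainder of recruitment. If only about 14 patients are left, the practical effect is small.
2. Reword the blinding sentence to say that all others are blinded to the code list, and that those who deliver the interventions or receive the assignments know the allocation. Data entry is the only other role that the article states as blinded, so no further role should be added unless the full protocol supports it.

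The cost is one new set of schedules, slightly looser balance within sites, and a wording change. No extra staff are needed.

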### Interventions

#### Neuromuscular electrical stimulation

NMES will be conducted three times a week during each dialysis session for 12 weeks. NMES will be performed as follows using a 4-channel functional electrical stimulation instrument (FES-1000/5000®, Stratec, Korea): impulse type: symmetrical biphasic, impulse width 400 μs, impulse frequency 60 Hz, and impulse on-off time 4–8 s. FES-1000 and FES-5000 are only different in batteries and provide the same electrical impulse. Participants will notify if there are any unpleasant symptoms. Impulse intensity will be individually adjusted to the maximum tolerated amperage for each stimulation session (impulse intensity range 0–100 mAp). Participants will be instructed to remain relaxed in a supine position with knees in extension during dialysis. Adhesive electrodes will be attached to a total of four areas of the bilateral lower extremities: vastus medialis: 3 cm above the upper border of the patella and 5 cm below the inguinal fold, vastus lateralis: 3 cm above the superior border of the patella and 5 cm below the inguinal crease toward the anterior superior iliac crest. NMES will be administered between 1 and 3 h after dialysis for 20 min during the first week and for an additional 2 min every week thereafter until 30 min (Fig. 2).

